## Abstract

**Background:**

Scientific research has consistently emphasised the high levels of stress encountered by family caregivers of individuals living with dementia. However, conventional self‐help approaches remain underutilised. The ‘Diversity‐On’ study addresses this issue. The study employs a storytelling approach to develop and evaluate an online self‐help program that is participatory and diversity‐sensitive, thereby ensuring congruence with diverse identities and lifeworlds.

**Methods:**

The study uses a mixed‐methods design, comprising the allocation and implementation of the intervention, the development of stories, a process evaluation (*N* = 20) and an outcome evaluation (quantitative: *N* = 130, qualitative: *N* = 20). The study's primary focus is its comprehensive participatory approach, integrated throughout the research process. The study is dependent on the input of a number of stakeholders, all of whom are committed to advocating for the concerns of patients.

**Discussion:**

Given its participatory methodology and intersectional perspective, the ‘Diversity‐On’ study is anticipated to yield a number of significant outcomes. The study has the potential to empower family caregivers of individuals living with dementia who are under high stress, empowering them to take part in self‐help groups despite multiple barriers, thus alleviating their burden. Additionally, it has the capacity to promote the well‐being of caregiving relatives who are providing care and are experiencing high levels of stress. The study's objective is to maintain home care arrangements for as long as possible, in accordance with the values and preferences of care recipients and their families. The study intends to develop and assess a customised online self‐help resource that is suitable for a diverse range of users and that remains accessible beyond the study period.

**Trial Registration:**

The project is subsequently registered in ClinicalTrials.gov

Summary
This is a protocol for a public health intervention, particularly in the area of nursing care, that aims to improve the health outcomes of the population, with a particular focus on vulnerable groups.The study can help to improve home care, maintain the setting and relieve the burden on the healthcare sector.The present protocol contains a detailed description of the hypotheses, rationale and methodology of the study to ensure transparency, reduce publication bias and enhance the reproducibility of study design and analysis.

## Introduction

1

As the number of individuals with dementia living at home is projected to rise worldwide, it is anticipated that there will be an increase in demand for home‐based care services as well (Prince et al. 2016). Family caregivers are expected to be the primary stakeholders providing essential support to their relatives (Ceci, Symonds Brown, and Purkis 2019). In Germany, the country in which this study will be conducted, 70% of individuals requiring care are cared for at home, with family members and relatives being the primary caregivers. Only 24.3% opt for outpatient care (Statistisches Bundesamt 2018). This proportion is lower than in many other industrialised nations, for example, Canada, where around half of the individuals living with dementia reside at home while receiving family support (Manuel et al. 2016). Particularly among individuals of Turkish origin in Germany, the percentage of those receiving home‐based care is considerably higher, at 98% (Okken, Spallek, and Razum 2008). As the number of individuals residing at home increases, so too will the demand for home‐based care. It is therefore evident that family caregivers will continue to play a significant role in maintaining the sustainability of the health and social care systems (Dawson et al. 2015).

For family caregiver providing care can often be physically and psychologically demanding (Kimura et al. 2019; Seidel and Thyrian 2019). In Germany, 48.7% of individuals involved in the provision of care for family members experience mental disorders, underscoring the considerable burden and subsequent consequences associated with caregiving responsibilities (Rothgang and Müller 2018). Mental illnesses represent the fourth leading cause of reduced healthy life years in Germany (Rabe‐Menssen, Dazer, and Maaß 2020), contributing significantly to the overall disease burden.

It is thus imperative that suitable assistance be made available to family caregivers in order to minimise the risks to their health, to prevent premature institutionalisation or substandard care for individuals with dementia and to sustain the effective functioning of health and social care systems (Schoenmakers, Buntinx, and DeLepeleire 2010). In order to support continuity of home care, it is essential that the primary caregivers have access to the necessary resources and that a properly functioning support network is in place. By enhancing the available resources for family caregivers, their individual coping strategies can be improved, leading to a substantial positive impact on their well‐being (Brügger, Jaquier, and Sottas 2016). In order to promote and protect the health of family caregivers, there is a need to focus on the cultivation of established coping mechanisms. A particular emphasis must be placed on the development of self‐management skills among family caregivers, with the objective of effectively mitigating the impact of various stressors (Oliveira, Sousa, and Orrell 2019; Huis In Het Veld et al. 2016). In light of the pivotal role of self‐management in the prevention of chronic diseases, it is evident that the empowerment of family caregivers is of paramount importance (Toms et al. 2015). Given that family caregivers are more susceptible to stress‐related chronic illnesses, the implementation of user‐oriented preventive measures is crucial to prevent diseases associated with overwork and burnout.

Support services such as traditional self‐help formats see limited uptake among specific population groups in Germany, including migrants (Kofahl et al. 2019). Consequently, the highly heterogeneous migrant population is particularly vulnerable in this context, as, for example, the proportion of people who are cared for at home is as high as 98% among people of Turkish origin in Germany. Qualitative studies conducted among the migrant community in German‐speaking countries, focusing on caregivers of individuals living with dementia, reveal that those caregivers choosing not to utilise support services or self‐help options can themselves become entangled in the ailment due to prolonged stress (Piechotta and Matter 2008). Research highlights that distancing themselves from their social environment can result in a distressing sense of isolation among family caregivers. Moreover, the fear of being stigmatised due to their caregiving responsibilities can further impede effective coping with both caregiving challenges and daily issues (Toms et al. 2015).

The risk of isolation and co‐illness could be mitigated through preventive and tailored interventions. These interventions should focus on addressing the caregivers' specific needs, enhancing their self‐management capabilities and empowering them through hands‐on support. By doing so, caregivers can regain a sense of control and autonomy. Directing one's attention away from stressful emotions, affording chances for relaxation and engaging with peers in comparable situations has the potential to alleviate the impact of responsibilities associated with caring for a loved one at home (Huis In Het Veld et al. 2016).

Currently, to the best of the authors' knowledge, no online self‐help platforms effectively cater to the diverse needs of migrants in Germany, despite the high prevalence of family caregivers within this population group who experience a high burden (Tezcan‐Güntekin and Razum 2018). Participants in a support group show considerable diversity in terms of age, life experiences, relationships with care recipients, religious beliefs, language proficiency, sexual orientation, educational attainment and the challenges associated with caring responsibilities. This heterogeneity has the potential to decrease the level to which individuals identify with their fellow group members, resulting in sporadic participation or even withdrawal from the group if differences are not appropriately addressed (Yılmaz‐Aslan et al. 2021). Consequently, online self‐help communities that are sensitive to this diversity must be established. Such an approach holds the potential to foster a substantial sense of belonging and continuity among participants, thereby maximising involvement within these groups.

Storytelling could be a beneficial strategy in self‐help groups (Greenhalgh 2017; Lewis 2011). This narrative approach holds significant potential for advancing health literacy, as well as bolstering self‐efficacy expectations and improving self‐management skills, particularly for family caregivers (Holm, Lepp, and Ringsberg 2005; Glodny, Yilmaz‐Aslan, and Razum 2011). The method entails arranging storytelling sessions that cover a wide variety of subjects, with the principal objective of enabling individuals to exchange information, personal encounters and perceptions (Glodny, Yilmaz‐Aslan, and Razum 2011). In a previous study by one of the co‐authors of the present paper ([name]), storytelling was implemented in the context of home care and was directed at Turkish immigrants. Within the study, a self‐help‐centred storytelling intervention was developed to provide family caregivers with a platform to freely discuss their caregiving circumstances and challenges they faced while sharing care‐related information. The methodology of generating narratives resulted in a significant exchange of knowledge, experiences and insights among the family caregivers involved. This highlighted techniques to minimise barriers to accessing support services and to maximise the unused potential for self‐help among family caregivers, while emphasising the fundamental importance of engaging the target audience in the design of such services (Kofahl et al. 2019).

As previously stated, self‐help formats are infrequently used by family caregivers of patients living with dementia. The objective of the ‘Diversity‐On’ study is to create an online self‐help platform that promotes diversity, encourages participation and takes into account the diversity of participants. This self‐help platform will establish a guided group specifically for caregivers of individuals living with dementia, utilising the previously mentioned storytelling methodology. The platform will be implemented for people with a Turkish migration background. This group is intended to serve as an example of a wide range of heterogeneous and diverse people who require individualised and diversity‐sensitive support, while also considering the intersectionality with other diversity characteristics. The online self‐help platform is designed to connect family caregivers who share common diversity characteristics or are in similar care situations, with a focus on enhancing their self‐efficacy. By doing so, it aims to alleviate the burden associated with their caregiving circumstances and expand their autonomy within their specific life contexts, ultimately strengthening their self‐management abilities.

Accordingly, the core research question of the ‘Diversity‐On’ study is: To what extent can a participatory and diversity‐sensitive online self‐help service, based on the storytelling approach, increase the self‐efficacy and reduce the burdens of caregiving relatives with a migration background, taking into account intersectional interrelationships with other diversity characteristics?

An outcome evaluation will determine the overall impact of the online self‐help service on self‐efficacy expectations and other related outcomes. As such, the study will examine the following primary and secondary hypotheses:

### Main (Primary) Hypothesis

1.1

The online self‐help service can increase the self‐efficacy expectation of family caregivers with Turkish migration background by 2.5 units (assessed with the SWE questionnaire; see Section 2).

### Secondary Hypotheses a–e

1.2

The online self‐help service canincrease dementia‐related health literacy,reduce perceived stress,improve health‐related quality of life,enhance empowerment,lessen perceived burden

of family caregivers with a Turkish migration background.

### Qualitative Hypothesis

1.3

The online self‐help service is presumed to have high usability.

### Trial Design

1.4

The study uses a mixed‐methods design, consisting of the allocation and implementation of the intervention, the development of stories, process evaluation (*N* = 20) and outcome evaluation (quantitative *N* = 130, qualitative: *N* = 20).

## Methods

2

This present protocol is reported in accordance with the reporting guidance provided by the SPIRIT checklist (Chan et al. 2013) (see Appendix 1), as recommended by the EQUATOR Network.

### Participants, Interventions and Outcomes

2.1

#### Study Setting

2.1.1

The study setting comprises the home care arrangements of individuals with dementia within the family unit. The principal objective of the study is to examine the processes involved in maintaining home care. The data will be collected in Germany, where the intervention will also be piloted and evaluated. It is reasonable to assume that the results can be applied internationally, and that the intervention can be applied in home care as well as in other care settings.

#### Eligibility Criteria

2.1.2

##### Study Participants

2.1.2.1

The objective of the intervention is to provide support to individuals of Turkish origin in Germany who are involved in the care of relatives living with dementia. The study will include all adults (aged ≥18 years) of Turkish origin who are responsible for the care of a relative living with dementia. Individuals who are not of Turkish origin, who are under the age of 18, or who are not responsible for the care of a relative living with dementia will be excluded from the study.

##### Council of Family Caregivers

2.1.2.2

The online self‐help program will be guided and facilitated by a council of family caregivers that will actively participate in the study. Comprising 10–12 family caregivers, the council will represent a diverse range across gender, class, race and body (Winker and Degele 2011). The council members will collaborate with the project team in the secondary data analysis (see below) and will also oversee the intervention. The study benefits from their participation by incorporating individual perspectives in the analysis and contributing to the participatory design of the research (von Unger 2014).

##### Expert Advisory Board

2.1.2.3

An additional expert advisory board will be established, consisting of nursing scientists, migration researchers, experts for health promotion and prevention, experts for participatory research and experts from the Turkish dementia community. The board will undertake ongoing, biannual monitoring and reflection of each study phase and interim findings.

#### Interventions

2.1.3

The ‘Diversity‐On’ intervention consists of an online self‐help platform that promotes diversity, encourages participation and caters to the diversity of the participants. This self‐help platform will facilitate a guided group specifically for caregivers of individuals living with dementia, utilising the previously mentioned storytelling methodology. The platform will be implemented for people with a Turkish migration background.

In total, 130 family caregivers will be allocated to 26 online support groups of about 5–6 persons each, comprising both intervention and control (as described below). The 26 groups will be randomised into an intervention and a control group, each comprising 13 groups.

[Intervention]: The individuals randomly assigned to the intervention group are divided into 6 groups of approximately 6 individuals, with each group representing specific diversity characteristics. In the intervention group, online self‐help sessions will be delivered using the previously mentioned diversity‐sensitive storytelling approach. The 6 intervention groups will convene on a monthly basis to discuss one story at each meeting. All participating co‐researchers of the intervention groups will receive prior training on the utilisation and management of the stories, as well as on the conduct of an online support group (opening, story presentation, discussion facilitation and closing).

[Control]: The individuals randomly assigned to the control group will also be randomly divided into 6 groups, comprising approximately 6 individuals each. The 6 control groups will convene on a monthly basis to conduct conventional support group sessions that are not storytelling‐based and that are not specifically tailored to the participants' diversity sensitivity.

The self‐help groups will be managed by members of the council of family caregivers. In order to ensure the ethical integrity of the study, all meetings of both the intervention groups and the control groups will be attended by one member of the project team.

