#### Sample Size

2.1.6

Given a power of 80%, an alpha error of 5% and a standard deviation of 4 in the primary outcome measure and an estimated intraclass coefficient of 0.15, a sample size of a total of 26 clusters, each consisting of 5–6 caregivers, makes it feasible to identify mean differences of 2.5 on the SWE scale. This constitutes a medium effect size (Cohen's *d* = 0.6). The primary and secondary hypotheses will be assessed through multivariate testing using structural equation modelling.

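### Section 2.1.3 gives both 13 and 6 groups per arm; the stated 80% power holds for 13, but would be about 44–52% if 6 groups of about 6 were run

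*Protocol article*

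**What the plan says.** Section 2.1.3 opens with 130 caregivers in 26 groups and continues: "The 26 groups will be randomised into an intervention and a control group, each comprising 13 groups".

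The two arm descriptions in the same section give another number. People assigned to the intervention "are divided into 6 groups of approximately 6 individuals". Those assigned to control "will also be randomly divided into 6 groups, comprising approximately 6 individuals each". Each description then has 6 groups of its arm meeting monthly. The figure 6 therefore appears four times: once for composition and once for meetings, in each arm.

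Elsewhere the document stays with the larger design:
- Section 2.1.6 bases its power statement on "a sample size of a total of 26 clusters" of 5–6 caregivers.
- Section 2.1.7.2 expects 130 evaluated caregivers from 156 recruited.
- Section 2.2.1 repeats 26 groups, 13 per arm.
- Section 2.3.3.1 describes 2 × 13 groups of 5–6.

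No section presents the 6 groups as a wave, phase or subset of the 13.

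**The concern.** In a cluster-randomised comparison, the number of clusters largely determines power. The sentences carrying the figure 6 are the ones that say how groups are made up and how many convene, so a team could follow them when setting up delivery. Doing so would give fewer than half the clusters on which section 2.1.6 relies. The trial would then have roughly an even chance, or less, of detecting the 2.5-point difference in the primary hypothesis, and a null result would say little. It would also provide places for about 72 people when 156 are to be recruited.

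This is not the kind of detail a statistical analysis plan would settle. The protocol states two incompatible numbers for the same quantity.

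**Working it through.** **Inputs, all from section 2.1.6.** Power and alpha: "Given a power of 80%, an alpha error of 5% and a standard deviation of 4 in the primary outcome measure". Correlation: "an estimated intraclass coefficient of 0.15". Target difference: 2.5 SWE points. Cluster size m: 5–6. The number of clusters per arm, k, is 13 or 6 according to which part of section 2.1.3 is used. The section does not state whether alpha is one- or two-sided. Two-sided is assumed, because it reproduces the stated 80%; one-sided 5% would give 86–90% at 13 per arm.

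**Formulas.**
- Design effect: DE = 1 + (m − 1) × 0.15
- Standard error of the difference: SE = 4 × √(2 × DE / (k × m))
- Normal power: Φ(2.5/SE − 1.96)
- t power: noncentral t with 2(k − 1) degrees of freedom and noncentrality 2.5/SE

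**The plan's own figure, 13 groups of 5 per arm.** DE = 1 + 4 × 0.15 = 1.60. SE = 4 × √(3.20/65) = 0.888. Ratio 2.5/0.888 = 2.82. Power is 80.4% (normal) or 77.1% (t, 24 df).

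**13 groups of 6 per arm.** DE = 1.75. SE = 4 × √(3.50/78) = 0.847. Ratio 2.95. Power is 83.9% (normal) or 80.8% (t, 24 df). The stated 80% therefore reproduces for 26 clusters.

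**6 groups of 6 per arm.** DE = 1.75. SE = 4 × √(3.50/36) = 1.247. Ratio 2.00. Power is 51.8% (normal) or 44.1% (t, 10 df).

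**Detectable difference at 80% power.** Under the normal approximation this is (1.960 + 0.842) × SE. The t figure solves the noncentral t for 80%.

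| Groups per arm × size | People in total | Power, normal | Power, t | Detectable, normal | Detectable, t |
|---|---|---|---|---|---|
| 13 × 5 | 130 | 80.4% | 77.1% | 2.49 | 2.59 |
| 13 × 6 | 156 | 83.9% | 80.8% | 2.37 | 2.47 |
| 6 × 6 | 72 | 51.8% | 44.1% | 3.49 | 3.88 |

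**Sensitivity for 6 groups per arm.**
- With 5 per group after dropout, power is 48.2% (normal) or 40.9% (t).
- With 6 per group and the t method, a correlation of 0.05 gives 57%, 0.10 gives 50% and 0.20 gives 40%.
- One-sided 5% gives 59% (t) to 64% (normal).

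None of these reaches 80%.

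**Which number fits the head counts.** 130/26 = 5 and 156/26 = 6, which matches groups of 5–6. 2 × 6 × 6 = 72 matches neither 130 nor 156.

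**The case against.** The strongest reply is that the 6-group wording is left-over text. It stands only in the two arm descriptions of section 2.1.3. The opening of that section and sections 2.1.6, 2.2.1 and 2.3.3.1 all give 26 groups or 13 per arm, and the head counts of 130 and 156 fit only 26 groups of 5–6. On that reading the correction is to wording and power is untouched. This largely stands: 26 groups is the better-supported design. It does not remove the contradiction, because the wording covers both arms and both composition and meetings, and nothing in the document marks it as superseded.

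Two stronger readings are tempting but not supported:
- A reader might infer that the protocol's 80% is wrong. It is not. Section 2.1.6 attaches it to 26 clusters, where it reproduces, and the document nowhere claims 80% for 12 groups.
- A reader might infer from the council of 10–12 caregivers (section 2.1.2.2) that 12 groups is the real plan, with one member for each. Section 2.1.3 says only that council members manage the groups. With monthly meetings, one member could manage several.

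The choice of method also matters. Setting only the t-based 44% against the stated 80% would be uneven, since the normal approximation that reproduces 80% at 5 per group gives 52% for 12 groups. Both figures belong in the statement.

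**Conclusion.** The contradiction is real and must be reconciled: section 2.1.3 gives 13 groups per arm and also 6 per arm. The power statement is sound for the design it names, 26 clusters of 5–6. The loss is conditional: only if 6 groups of about 6 per arm were actually run would power for 2.5 points drop to about 44% (t, 10 df) to 52% (normal), with a detectable difference of about 3.9 or 3.5 points respectively.

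These figures rest on two-sided 5%, the protocol's SD of 4 and correlation of 0.15, equal group sizes, and no dropout in the 6 × 6 case. The document does not show which number the team intends to run.

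**What to change.** In section 2.1.3, replace 6 groups by 13 groups of 5–6 in both arm descriptions and in both sentences on monthly meetings.

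In the same edit, align the order of assignment with section 2.2.1. There, and in the opening of 2.1.3, groups are formed first and then randomised, whereas the arm descriptions assign individuals to an arm and then divide them into groups. Changing the number alone would leave that conflict. Section 2.2.2 also puts the arm before the small group, so it should be checked at the same time.

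If 12 groups is the real plan, restate section 2.1.6 as about 44–52% power for 2.5 points (detectable difference about 3.5–3.9 points), and correct the group numbers in sections 2.2.1 and 2.3.3.1, the opening of 2.1.3, and the 130 and 156 in section 2.1.7.2.

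The first route costs only a wording amendment. The second costs a much less favourable power statement.

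### The 26 groups draw their leaders from a council of 10–12, so some must share a leader, yet the power calculation treats all 26 as independent clusters

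*Protocol article*

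**What the plan says.** Section 2.1.3 (Interventions) says the self-help groups "will be managed by members of the council of family caregivers". The sentence names no arm and comes after the descriptions of both arms. The Discussion repeats that council members guide the groups. On the size of the council, Section 2.1.2.2 says: "Comprising 10–12 family caregivers, the council will represent a diverse range across gender".

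Section 2.1.6 bases the sample size on "a sample size of a total of 26 clusters, each consisting of 5–6 caregivers", with "an estimated intraclass coefficient of 0.15" and no other level of clustering. Section 2.1.3 says: "The 26 groups will be randomised into an intervention and a control group, each comprising 13 groups". Sections 2.2.1 and 2.3.3.1 repeat the 13 per arm. Section 2.1.3 also describes 6 intervention groups and 6 control groups, which does not agree with 13 per arm.

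Story training is given to the co-researchers of the intervention groups (2.1.3). Council members also take part in analysing the interviews from which the stories are built (2.1.2.2, 2.3.1). Control sessions are to be free of storytelling (2.1.3).

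**The concern.** Groups led by the same person share that person's skill and style, so their mean outcomes may move together. An ICC for members of one group covers resemblance within that group. It does not cover resemblance between two groups with the same leader, however generously it is set.

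Two things are at stake, and they belong to different layouts. If each member leads groups in one arm only, the replication behind each arm mean is nearer to 5–6 leaders than to 13 groups. An analysis that ignores this understates the standard error. If members lead groups in both arms, the leader effect largely cancels from the comparison, but someone trained in the stories may then run a control group, which could narrow the contrast between arms. The article does not say which layout applies.

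**Working it through.** **Inputs from the article.** SD 4, difference 2.5, power 80%, alpha 5% (two-sided assumed), ICC 0.15, and 13 groups per arm of 5–6 people (2.1.6, 2.1.3). Council of 10–12 (2.1.2.2). I take m = 5 per group, since 130/26 = 5.

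**Assumption not in the article.** The facilitator share of total variance, ρf, is taken as 0.02–0.10. Total ICC stays at 0.15, so ρf is a part of it and not an addition to it.

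**The plan's own figure.**
- Unclustered n per arm = 2 × [4 × (1.960 + 0.842)/2.5]² = 40.19.
- Design effect = 1 + (5 − 1) × 0.15 = 1.60.
- 40.19 × 1.60 = 64.3 per arm; 64.3/5 = 12.86, rounded up to 13 groups per arm, or 26 groups and 130 people.
- Power with 13 per arm is 80.4% by the normal approximation and 77.1% by a t test on 24 df.

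The stated sample size therefore reproduces, with almost no slack and with all 26 groups taken as independent.

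**Sharing.** 26/12 = 2.17 and 26/10 = 2.6 groups per member.

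**Layout A: facilitators nested in arm (5 or 6 per arm).** Design effect = 1 + (m − 1) × 0.15 + (g − 1) × m × ρf, where g is the sum of squared numbers of groups per leader, divided by 13.
- Five leaders (3, 3, 3, 2, 2 groups): g = 35/13 = 2.69.
- Six leaders (3, 2, 2, 2, 2, 2 groups): g = 29/13 = 2.23.
- Example, five leaders, ρf = 0.05: 1.60 + 1.692 × 5 × 0.05 = 2.02.

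The standard error is 4 × √(2 × design effect/65). Power is from the noncentral t. Type I error is simulated for a t test on the 26 group means that ignores the leader.

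| Leaders per arm | ρf | Design effect | Power, leader-level df (8 or 10) | Power, 24 df | Type I error, leader ignored |
|---|---|---|---|---|---|
| 5 | 0.02 | 1.77 | 65% | 73% | 6% |
| 5 | 0.05 | 2.02 | 60% | 67% | 8% |
| 5 | 0.10 | 2.45 | 52% | 59% | 12% |
| 6 | 0.02 | 1.72 | 69% | 74% | 6% |
| 6 | 0.05 | 1.91 | 64% | 70% | 7% |
| 6 | 0.10 | 2.22 | 58% | 63% | 10% |

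Part of the loss comes from the degrees of freedom alone: at ρf = 0, power on 8 or 10 df is already 70% or 72%.

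**Layout B: facilitators spread over both arms (10 or 12 in all, each leading in both).** The same naive test was simulated.

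| ρf | Type I error | Power |
|---|---|---|
| 0.02 | 4% | 78% |
| 0.05 | 3% | 79% |
| 0.10 | 2% | 81% |

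**The 6 + 6 reading of 2.1.3.** Twelve members could lead one group each, though 10 or 11 could not. That leaves 12 clusters, with power of 48–52% (normal) or 41–44% (t) for groups of 5–6.

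**The case against.** The strongest reply is that the harm depends on the layout. Inflated error and lost power need leaders confined to one arm, while contamination needs leaders who cross arms. Both cannot apply in full, and under crossing the naive test errs on the safe side. This stands, and it is why no single direction is claimed here.

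The other objections stand in part:
- The article gives no facilitator variance, and the problem vanishes if it is zero. The figures are a sensitivity range and not an estimate.
- Section 2.1.6 names structural equation modelling, not a t test on group means. The simulated error rates show what ignoring the leader can do; they do not describe the planned analysis.
- The 26 groups are themselves in doubt, because 2.1.3 also gives 6 + 6. That reading avoids sharing only with a full 12 members, and it does not rescue the power.
- The Discussion speaks of oversampling the council, so 12 may not be a hard ceiling, and co-leading or rotation is possible. Neither would by itself make the groups independent.
- Story training for co-researchers of the intervention groups hints at arm-specific roles, but does not rule out crossing.
- A rota and model details commonly sit in the full protocol or SAP, so their absence here is not the finding. The finding is that the cluster count and the staffing, both stated in this article, do not fit together as independent units.

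A reader might go further and infer that the trial's real replication is 5–6 leaders per arm, or that its standard errors are certainly too small. The article does not support either, because it does not say that leaders are confined to one arm.

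**Conclusion.** The point holds in a limited form. The arithmetic in 2.1.6 is right, but it rests on 26 mutually independent groups, and a council of 10–12 cannot give 26 groups a separate leader each. The error bars may be wrong in either direction: too narrow under nesting (type I error about 6–12%) and too wide under crossing (about 2–4%). Under nesting, an analysis on facilitator-level degrees of freedom would have about 52–69% power, compared with 77% (t) or 80% (normal) under independence. All of this assumes ρf of 0.02–0.10, a total ICC of 0.15, five per group and one fixed leader per group. It is worth correcting because the remedy is cheap and because who led which group may be hard to reconstruct afterwards.

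**What to change.** 1. Reconcile 13 versus 6 groups per arm in Section 2.1.3, since everything else depends on that count.
2. State there how council members are assigned to groups and arms.
3. Record a facilitator identifier for every group, including any change of leader.
4. Include facilitator as a level in the primary model, nested or crossed as actually assigned, with small-sample degrees of freedom.
5. State in Section 2.1.6 that 80% power assumes no correlation between groups sharing a facilitator, and give power over a stated range of facilitator variance.

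Whether each member should lead in one arm only is for the investigators to decide. That rule would limit contamination, but it creates the nested layout and its loss of power. It also cannot undo the council's shared work on the story source material.

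The cost is one more variable, one more model term and possibly a lower stated power.
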